**Statistical And Analytic Plan**

**Focus Groups:** Thematic analysis

**Cluster-Randomized Trial:**

- Primary: Longitudinal pre-post analysis to detect impact of program on dose of opioid and opioid discontinuation
- Secondary: Rate of falls

**Web-based surveys:** Descriptive statistics

---

**DATA AND SAFETY MONITORING PLAN**

This study will not have a separate data safety monitoring board. This decision was made because the intervention is usual care that is provided from the clinics. If there are incidents related to deprescribing the clinics will follow their protocols and refer patients to urgent care, the emergency room or have an on-call provider call the patient back. This is usual care. Information about adverse effects will be reported to the PI during the monthly check in. Side effects from discontinuation are a known risk from deprescribing opioids and BZDs, therefore they will be dealt with through the typical care system, which includes evening and weekend call hours for primary care clinics, access to the emergency department, and other standard care options for patients. The PI will follow up with the prescriber once notified to ensure that the usual care for handling side effects from discontinuation were followed.

---

## 1 BACKGROUND AND RATIONALE

### 1.1 Introduction

Falls among older adults in the US account for 2.8 million injuries, 800,000 hospitalizations, and 28,000 deaths per year. US medical costs associated with falls now total approximately \$50 billion. More than 150 randomized trials document successful falls interventions. Observational studies show consistent associations between falls and certain medications. Thus, it is widely accepted that fall-related morbidity and mortality could be reduced if systems were in place to identify and intervene in falls risk. Unfortunately, most physicians do not routinely screen older patients for falls and with the shortage of physicians going into primary care, it is unlikely that screening will improve.

The University of North Carolina at Chapel Hill (UNC) School of Pharmacy pioneered an approach using community-based pharmacists to screen and identify older adults at risk. In our study, pharmacists identified 186 patients who were on a high-risk medication. Pharmacists then conducted a medication review using a clinical algorithm to guide the decision-making process. Twenty-five percent of the pharmacists' recommended medication changes were accepted by physicians. In our current, follow-up, CDC-funded study, the UNC Schools of Pharmacy and Medicine are using an enhanced service network of 65 pharmacies to mitigate the barriers faced by community pharmacists conducting medication reviews. As of March 1, 2018, 70% of qualified patients were screened by pharmacists and 56% received a medication review with recommendations for lower risk drugs. Of these, 35% of have been accepted by prescribers. These studies show that other members of a healthcare team,

specifically, pharmacists, can accurately identify older adults at risk for falls and communicate recommendations for medication changes.

## 1.2 Potential Risks and Benefits

There are three primary methods used for this study: focus groups, web-based surveys, and a cluster-randomized trial. The risks from focus groups and web-based surveys are minimal and primarily involve the possibility of loss of confidentiality and participants feeling uncomfortable.

The primary risk for the cluster-randomized study is potential withdrawal symptoms from discontinuation of opioids and BZDs. This risk is part of the standard of care associated with opioid and BZD management and is no greater than the normal risk experienced with standard patient care. The goal of this study is to better inform clinicians as to the fall-related risks associated with elderly patients' use of opioids and BZDs as well as best practices for tapering patients off opioids and BZDs without excess risk. If a clinician deems the falls-related benefit from reducing or stopping an opioid or BZD outweighs the risk associated with withdrawal, they can work with a patient to reduce or stop their medication. As such, potential benefits to the patient include a reduced risk of falls, which are associated with substantial morbidity and mortality in older adults.

## 1.3 Relevant Literature and Data

**Prevalence and Consequences of Falls among Older Adults.** Falls are the leading cause of unintentional fatal and nonfatal injury among adults age 65 and older in the US. According to the latest figures, one in four older adults fall each year. Outcomes associated with falls and fall-related injuries include: functional impairment, loss of independence, emotional distress, and increased use of health and social services. Fractures, particularly hip fractures, are the most common and expensive nonfatal fall-related injury, accounting for about one-third of fall injuries and 60% of associated medical costs. Reducing the burden of falls among older adults is a significant public health challenge.

**Medication Management and Falls.** Past research demonstrates that individuals who use multiple medications are at increased risk for falls. In observational studies, consistent associations have been found between the use of high-risk medications such as opioids and benzodiazepines (BZD) medications and an increased risk of falls. Prior research has demonstrated that pharmacists can significantly reduce or eliminate medications that place patients at high risk of falls by performing medication reviews. However, researchers conclude that medication reviews alone do not lead to a reduction in overall falls. In our experience, opioid and BZD classes of drugs are the most difficult to manage in patients. Therefore, research focusing on medication management of opioids and BZDs is necessary to reduce falls among older adults.

A literature review of 239 peer reviewed articles revealed several studies citing the link between high-risk medications and falls and subsequently calling for deprescribing algorithms and education. The first tool for deprescribing these medications was the Beers Criteria published in 1991. Mark Beers and a panel of experts created a list of potentially inappropriate medications for older adults. While the use of many Beers list medications declined, implementing the list as a stand-alone resource, without educational support, lead to an overly rigid application, essentially demonizing even the appropriate use of these medications in some settings.

In 2011, the Canadian guideline for safe and effective use of opioids for chronic non-cancer pain gave specific deprescribing advice to family physicians. An implementation of a deprescribing protocol in Japan resulted in pharmacists recommending medication changes 48% of the time (310 out of 651 medications reviewed). Ultimately, 292 medications were changed. This matches the experience of a previous randomized controlled trial conducted by one of the co-PIs. In this trial, 186 patients with a

history of falls who were taking high-risk medications received either a face-to-face medication consultation at a community pharmacy or usual care. Those in the treatment group were more likely to discontinue the use of a high-risk medication or have their dosages reduced.

Over time, researchers have added patient education and non-pharmacological strategies as active interventions in deprescribing protocols so that clinicians have more than just a list of prohibited medications to work with. A 2010 study of 591 community dwelling older adults prescribed BZDs or a related drug showed that instructing patients on how to discontinue these medications and why they should do so prompted a 35% reduction in use, while the control group, which received no such instructions, increased their use by 4%. An inpatient study in Ireland found only 20% of falls risk medications were suitable for change. Given that medication reviews were time consuming, the researchers recommended targeting certain medications.

Keeping patients from resuming the use of BZDs or opioids over the long term is also a challenge. A meta-analysis of 18 randomized trials found moderate success in deprescribing psychotropic medications. Four of these projects reported falls outcomes. One of the studies reported a 66% reduction in falls, but 47% of patients resumed the use of the medications; therefore, clinicians need a strategy of long-term interventions.

The literature shows progression over time in our awareness of the role of medications in falls and an increasing sophistication of interventions, including successful interventions in pharmacies. Policy makers and payers are starting to support these efforts. The Centers for Medicare and Medicaid Services regulations including Medicare Part D now require medication reduction strategies and numerous quality improvement projects focus on reducing high-risk medications to prevent falls.

**Engaging the Entire Health Care Management Team in Falls Prevention for Older Adults.** The American Geriatrics Society/British Geriatrics Society Clinical Practice Guideline for Prevention of Falls in Older Persons recommends that healthcare providers (HCPs) ask all older adults about falls, their frequency of falling, and difficulties in gait or balance on an annual basis. However, this screening occurs infrequently in clinical practice. For example, in one study, only 25% of older adult patients reported they had been asked about falls annually and only 48% reported they had ever been asked about falls. Another study, based on a nationally-representative sample of Medicare beneficiaries, found that less than 30% of the individuals who had experienced a fall within the previous year had received counseling about fall prevention from their health care provider. We could only find one study that engaged the entire health care team in reducing the risk of falls. Engaging the entire health care team may help patients adopt and maintain behaviors that reduce falls risk especially as it relates to opioid and BZD deprescribing. Regarding deprescribing, only a few studies focus on a patient centered approach including education and cognitive behavioral therapy in addition to deprescribing. This study will use a team-based approach to screen patients and de-prescribe opioids and BZDs for patients at risk for falls in the outpatient setting.

**Impact of Proposed Study.** This will be one of the first cluster-randomized studies targeting deprescribing of opioids and benzodiazepines in outpatient clinics with the intent to reduce falls in older adults. Implementing a multidisciplinary deprescribing educational toolkit within 10 outpatient clinics will promote replication and expansion, significantly reducing falls in the target population. Ultimately, this toolkit can be distributed to outpatient clinics nationally.

## 2 STUDY OBJECTIVE

**AIM 1:** Use EHR data to inform primary care outpatient clinics of older adults who are at high risk of falls due to the chronic use of opioids and/or BZDs. Once alerted, clinics will use a team-based approach to screen and plan falls interventions focused on deprescribing.

**AIM 2:** Develop and implement a proactive deprescribing medication guidance document with supporting resources (toolkit) for older adults on opioids and/or BZDs.

**AIM 3:** Evaluate (a) the utilization of the deprescribing toolkit in practice; (b) the satisfaction of clinic teams with the toolkit; (c) the impact of the toolkit on opioid and BZD exposure (primary outcome variable); (d) the rate of falls (secondary outcome variable).

## **2.1 Primary Objective**

**Focus Groups:** To inform the development and refinement of the opioid and benzodiazepine deprescribing toolkit (guidance document with supporting resources) and associated algorithm.

**Web-Based Survey:** To capture provider-reported barriers to and facilitators for the provision of deprescribing services as well as provider-reported demographics.

**Cluster-Randomized Trial:** To reduce opioid and BZD exposure, as measured by dose and discontinuation rate.

## **2.2 Secondary Objective**

**Cluster-Randomized Trial:** To evaluate the rate of falls.

# **3 INVESTIGATIONAL PLAN (brief overview)**

## **3.1 Study Design**

This study consists of three distinct sets of methodologies: focus groups, a web-based survey, and a cluster-randomized trial.

### **3.1.1 Focus Groups:**

The patient focus group will be conducted in-person. The patient focus group participants will be asked open-ended questions around the following themes: (1) their attitudes toward use of opioids or BZDs to manage chronic pain or sleep respectively; (2) what level of concern do they have, if any, with respect to dependence on their medications; (3) what level of concern, if any, do they have with respect to the risks of overdose; (4) what experiences have they had with withdrawal attempts or symptoms; (5) what other therapies are they are aware of; (6) what other therapeutic approaches have they tried/or would they try; (7) what barriers, if any have they experienced in using alternative therapies; and (8) what knowledge do they have about the correlation between their medications and the risk of falls. Audio recordings will be transcribed and thematically coded. To ensure anonymity, names will not be recorded, and tapes will be destroyed immediately after transcription. Study participants may receive nominal compensation as well as transportation reimbursement. Three independent coders will review the tapes. During coding, three coders will 1) study the textual material; 2) pinpoint recurring quotes; 3) examine them vis-à-vis related or contradictory quotes also in the text; and 4) organize them into major themes. As part of axial coding, the coders can compare notes and negotiate themes that provide the richest understanding of the study participants' knowledge and experiences.

The provider focus group will also be conducted in-person. The provider focus group interviews are designed to collect information regarding providers' deprescribing practices. Specifically, 1) their attitudes about prescribing opioids and/or BZDs for their patients; (2) what recommendations they have for reducing the dosage of opioids and/or BZDs; (3) what recommendations they have for adjunctive therapies that can help support reducing the dosage; (4) what concerns they have in terms of dependence, withdrawal and/or overdose for their patients; and (5) what barriers, if any, they have experienced when recommending alternative therapies. The interviews will be guided by a standardized interview protocol. All interviews will be audio-taped to facilitate planned content analyses. We anticipate that the focus group interviews will take approximately 2 hours to complete. Resulting transcripts will be analyzed similarly to the patient focus group interviews.

### 3.1.2 Web-Based Survey:

We will collect primary data via a web-based survey of all health care providers within the intervention and control clinics. The web-based survey will be distributed at two different time points: 1) after clinics have been randomized into intervention and control groups but before the intervention is implemented; and 2) after the trial has been completed. The purpose of the survey is to collect information on the intervention's effectiveness.

We estimate that each clinic will employ an average of six health care providers. Thus, we estimate that we will request approximately 120 health care providers (6 providers per clinic x 20 clinics) to complete the survey. The survey will solicit information that is easily quantified (e.g., basic demographic data, terminal professional degree, clinic volume, perceived barriers to deprescribing services, and provider knowledge, skills and attitudes about deprescribing). We anticipate that the web-based survey will take an average of 15 minutes to complete.

Providers will not receive the survey until after randomization has occurred. A clinic's eligibility for randomization into the trial or continued participation in the trial is completely independent of whether or not any clinic providers respond to the survey.

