| Study Design                                                 | This mixed method study incorporates two distinct study designs. Focus groups will be used to inform the development and refinement of a deprescribing guidance document with supporting resources. This document will define the provider-focused educational intervention which will be tested using a cluster-randomized design . Eligible providers will be randomly assigned to intervention and control groups. Impact of the educational intervention on medication use and falls will be assessed using an longitudinal pre-treatment post-treatment design , with patients receiving care from control clinics serving as a quasi-equivalent comparison group. Data from clinics will also be supplemented by a web-based survey , which will be given twice: prior to the start of the study and after its completion.                                                                                                                                        |
| Subject Population key criteria for Inclusion and Exclusion: | Inclusion Criteria: To be eligible to participate in the study, clinics need to be affiliated with UNC HealthCare and have a patient population that includes patients 65 years of age or older. The educational intervention will target patients at least 65 years old and taking at least one opioid or benzodiazepine medication listed                                                                                                                                                                                                                                                                                                                                                                                                                                                                                                                                                                                                                                                         |

---

in the design section for > 6 weeks, indicating they are at high risk for falls.

To be eligible to participate in the patient focus group, participants need to be a patient in one of the intervention group clinics, 65 years of age and older, and taking at least one opioid or benzodiazepine chronically.

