### **4.2 Screening/Baseline Visit Procedures and Observation Procedures for the Cluster-Randomized Trial:**

- (1) Randomize intervention and control clinics:** A list of clinics that are interested in participating will be compiled by the primary investigators. A member of the study team, [name], PhD, will use the random number generator built into SAS to randomize 10 clinics into treatment and 10 clinics into control groups. If the number of potentially eligible clinics exceeds 20, 20 clinics will be chosen at random, and this list will subsequently be divided into 10 random treatment clinics and 10 random controls. Results of randomization will be provided to the study coordinators, who will inform clinics of their status.

Data for all patients who meet inclusion criteria will be included in this analysis. This educational

intervention is intended to better inform providers in intervention clinics as to the fall-related risks associated with opioids and BZDs as well as best practices in deprescribing opioids and BZDs. A toolkit to support screening and deprescribing will also be provided to providers at intervention clinics. It is expected that providers will use this information to attempt deprescribing for any patients for whom they feel the benefits of deprescribing outweigh the risks. The study team will collect data from the EHR on all potentially eligible patients, regardless of any attempted deprescribing. The same data will be collected for patients who received care from treatment and control clinics.

**(2) Screen for risk of falling:** Intervention group clinics will be expected to screen all patients who appear on the baseline report for falls risk, questions if the patient has not already been screened previously, by using the STEADI screening questions. Each clinic will be allowed to determine how they will integrate these questions into the patient care process. Although the processes used to integrate the screening questions into patient care will vary across clinics, all clinics will be required to enter patient responses to the questions into the EHR, as is standard practice in all UNC HealthCare clinics.

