## 6 STATISTICAL CONSIDERATION

Statistical considerations are described below for the primary and secondary outcomes from the cluster-randomized trials. No statistical analysis will be conducted with focus groups, and the surveys will be analyzed using descriptive statistics and bivariate assessments for pre-post change in provider knowledge, skills, and attitudes in management of opioids and BZDs between intervention and control clinics.

All hypothesis tests that are observed and deemed to be not statistically significant will be reported as being inconclusive. All statistical estimates of population parameters will be tabulated along with corresponding confidence intervals (CIs) and/or standard errors (SE). All hypothesis tests and tests for power are two-sided with an overall alpha of 0.05, unless otherwise specified.

**6.1 Primary Outcomes: Opioid and BZD exposure,** as defined by changes in milligram equivalents over time across control and intervention groups as well as discontinuation of opioids or BZDs. Outcomes are described in more detail in Section 6.3.

**6.2 Secondary Outcomes: Risk of Falls,** as defined by differences in rate of falls over time across control and intervention groups and described in more detail in Section 6.3.

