## 10 CONSENT PROCESS

Clinics: [name], with other team members from the UNC Medical School, will reach out to key stakeholders in the targeted clinics (practice managers and/or physicians). They will provide a letter of invitation to participate in the study and will meet with these key stakeholders in person to discuss any questions the stakeholders have about the nature of the study, procedures, risks, and benefits. A copy of the study's IRB application will be provided to these stakeholders if requested. Each clinic's 'study champion' will be asked to sign a consent form prior to the clinic's participation. Consent from clinic patients will not need to be obtained since the study's intervention will be focused on educating providers on improving their delivery of the standard of care.

Providers in participating clinics, who will be asked to complete two web-based surveys, will be provided a written consent form that they will need to submit electronically prior to being able to access the survey questions. This consent form will include a written statement stating that their participation in the survey is voluntary and by completing the survey they are consenting to participate. The consent form will also delineate the nature of the study and the risks and benefits of participating.

Focus group participants will be provided a written consent form that they will need to sign prior to the start of the focus group session. The consent forms will delineate the nature of the study and the risks and benefits of participating in the focus group.

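### The baseline provider survey goes out only after randomisation, and nothing requires it to close before clinics learn their arm, so the between-arm comparison of provider change lacks a protected baseline

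*Protocol*

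**What the plan says.** Protocol section 3.1.2 times the first survey "after clinics have been randomized into intervention and control groups but before the intervention is implemented", and adds a rule that excludes earlier release: "Providers will not receive the survey until after randomization has occurred". It gives the aim of the survey as follows: "The purpose of the survey is to collect information on the intervention's effectiveness".

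Section 6 plans descriptive statistics for the survey and also "bivariate assessments for pre-post change in provider knowledge, skills, and attitudes in management of opioids and BZDs between intervention and control clinics". The first survey is therefore the baseline term of a between-arm contrast.

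On disclosure, section 4.2(1) says: "Results of randomization will be provided to the study coordinators, who will inform clinics of their status". It does not say when this happens relative to the first survey. No masking of providers is described.

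Section 10 tells providers that "their participation in the survey is voluntary and by completing the survey they are consenting to participate". Section 3.1.2 makes a clinic's eligibility and continued participation independent of whether its providers respond. Section 4.1 recruits both the patient and the provider focus groups (12 people each) from intervention clinics before the intervention is implemented.

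**The concern.** Self-reported attitudes, skills and perceived barriers are open to influence from what the respondent expects to happen next. A provider told that the clinic is about to be trained in deprescribing may answer differently from one told that the clinic is a control, and may be more or less inclined to answer at all. Either effect makes the two arms differ at baseline for a reason other than chance, and the difference carries into the comparison of change.

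The provider focus group could add to this in one arm only. Its topics in section 3.1.1 (attitudes to prescribing, recommendations for reducing dose, barriers to alternatives) overlap with the survey content.

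At stake is the credibility of the provider-level evidence on whether the intervention changed knowledge, skills and attitudes. Once clinics have been told their arm, no later analysis can recover a baseline unaffected by that knowledge.

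**Working it through.** **Order of events.**

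| Step | Where | What is fixed |
|---|---|---|
| Randomise clinics 10:10 | 4.2(1) | Before survey 1 |
| Tell clinics their status | 4.2(1) | No timing relative to survey 1 |
| Survey 1 | 3.1.2 | After randomisation, before the intervention |
| Focus groups from intervention clinics | 4.1 | Before implementation; no timing relative to survey 1 |
| Survey 2 | 3.1.2 | After the trial |

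Both orders, disclosure then survey or survey then disclosure, comply with the text. The independence of eligibility from response keeps the survey from influencing randomisation. It does not keep knowledge of the arm from influencing the survey.

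**Number surveyed.** Section 3.1.2: 6 providers × 20 clinics = 120, as stated. With 10 clinics per arm that is 60 providers per arm.

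**How a shift enters the contrast.** Let knowledge of the arm move mean answers in one arm by b₀ at survey 1 and b₁ at survey 2, in SD units. The bias in the between-arm difference in change is b₁ − b₀. If the shift is confined to baseline (b₁ = 0), the bias is the full −b₀. If it persists unchanged, it cancels.

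**Size, for the case b₁ = 0.** Inputs not in the protocol, taken as assumptions: b₀ of 0.2 to 0.3 SD; pre-post correlation ρ = 0.5; response of 50% or 100%; intraclass correlation of the change score of 0 or 0.1. The test is two-sided at 0.05 (section 6).

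SE = √[DE × 2 × 2(1 − ρ)/n], with n respondents per arm and DE = 1 + (m − 1) × ICC for m respondents per clinic.

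- Full response, no clustering: √(2 × 2 × 0.5/60) = 0.183. Then 0.2/0.183 = 1.1 and 0.3/0.183 = 1.6 standard errors.
- Full response, ICC 0.1, m = 6: DE = 1.5, SE = √(1.5 × 2/60) = 0.224. Ratios 0.9 and 1.3.
- 50% response (n = 30), no clustering: SE = √(2/30) = 0.258. Ratios 0.8 and 1.2.
- 50% response with ICC 0.1, m = 3: DE = 1.2, SE = √(1.2 × 2/30) = 0.283. Ratios 0.7 and 1.1.

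Varying response and clustering one at a time gives roughly 0.8 to 1.6 standard errors; both together take the lower end to about 0.7.

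**Effect on the test when the true effect is zero.** False-positive rate = 1 − Φ(1.96 − b₀/SE) + Φ(−1.96 − b₀/SE):

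| Scenario | b₀ = 0.2 | b₀ = 0.3 |
|---|---|---|
| Full response, no clustering | 19.5% | 37.6% |
| Full response, ICC 0.1 | 14.5% | 26.9% |
| 50% response, no clustering | 12.1% | 21.3% |
| 50% response, ICC 0.1 | 10.9% | 18.5% |

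The nominal rate is 5%. The clustered rows assume that the analysis allows for clustering. These figures cover shifted answers only; differential non-response is not quantified.

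**The case against.** The strongest reply is that randomisation and disclosure are separate steps. A reader might infer from section 3.1.2 that providers answer the first survey already knowing their arm. The text does not say so, and a coordinator could follow it to the letter and still collect every response before any clinic is told. That stands: the defect is a missing safeguard, not a stated unmasked baseline.

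A reader might also infer a contradiction with the synopsis, which describes the survey as "which will be given twice: prior to the start of the study and after its completion". That wording is looser than section 3.1.2 but compatible with it, since a survey sent after randomisation and before the intervention can fairly be called pre-study.

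The survey is also peripheral. Section 2.1 gives its objective as barriers, facilitators and demographics, the synopsis lists only descriptive statistics for it, and section 6.4 makes no power claim for it. The primary and secondary outcomes come from the EHR. All of this limits the weight of the point. It does not remove the between-arm comparison in section 6 or the effectiveness purpose in section 3.1.2.

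A subtler argument is that survey 2 is unavoidably answered with the arm known. If that knowledge shifts answers by the same amount both times, an unmasked baseline cancels the shift and a masked one lets it through. This is correct for a persistent reporting shift. It does not cover anticipation that fades or a difference in who responds, and it gives no reason to leave the order to chance.

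Finally, the 0.2 to 0.3 SD shift has no source in the documents, and even its upper ratio of 1.6 is below 1.96, so the shift alone would not be expected to produce a significant result. It would raise the false-positive rate, not determine the outcome.

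**Conclusion.** The concern holds in a limited form. The protocol sets the first survey after randomisation, uses it as baseline for a between-arm comparison of change, has clinics told their status, and does not require the survey to close first. Baseline answers and voluntary response may therefore depend on known allocation.

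The size of any bias is unknown. The figure of roughly 0.8 to 1.6 standard errors rests on an assumed shift of 0.2 to 0.3 SD present at baseline only, a pre-post correlation of 0.5, and the response and clustering values above.

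The focus-group contribution is less certain. Section 3.2 places focus groups in Year 1 and randomisation in Year 2, whereas section 4.1 draws the groups from intervention clinics, so the actual order is unclear.

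It would be wrong to conclude that the main trial result is at risk: opioid and BZD exposure and falls are taken from the EHR (section 5) and do not depend on the survey. The point deserves correction because the gap can be closed by scheduling beforehand and cannot be repaired afterwards.

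**What to change.** Amend sections 3.1.2 and 4.2(1) so that:

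1. Survey 1 is sent and closed after a clinic has agreed to take part and, if more than 20 clinics are eligible, after the 20 have been chosen.
2. It closes before the clinic's allocation is disclosed, and before focus-group participants are recruited from intervention clinics. Align sections 3.2 and 4.1 on when that recruitment happens.
3. Eligibility and continued participation stay independent of response, as now written.
4. The survey 1 response rate is reported by arm.

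The release rule in section 3.1.2 then needs rewording, because what matters is disclosure, not the random draw. The survey may fall before or after the draw provided that clinics have not been told the result.

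The cost is a short delay in telling clinics their status and in starting focus-group recruitment, which feeds revision of the toolkit. The survey takes about 15 minutes online and nothing is added to it. The change cannot remove any effect of knowing the arm on survey 2, so the report should state that follow-up answers were unmasked.
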